## Abstract

Remote ischemic conditioning represents an intervention based on blood flow reduction applied at a distance from the lesion. The mechanism is supposed to elicit neurovascular protection, anti-inflammatory action, reduced excitotoxicity and metabolic protection. This study aims to explore the efficiency and safety of remote ischemic conditioning during the first five days following in patients who are ineligible for reperfusion treatment (intravenous thrombolysis or/and mechanical thrombectomy). We hypothesized that this intervention would reduce the infarct size (neuroprotection in the reperfusion window) and improve functional recovery. We aim to conduct a double-blind controlled trial, multicenter in two hospitals in Romania. Two hundred patients with acute ischemic stroke randomly divided into an experimental group and a control group will be included. The subjects in the experimental group will be subjected to remote ischemic conditioning twice daily with a maximum of 180 mmHg for 5 days, and a guideline- based treatment as well. The subjects in the control group will receive cuff inflation to 30 mmHg, which will induce sham preconditioning. The primary outcome measure will be radiological - the difference between baseline brain infarct volume and the volume at 180 days in the experimental group versus the control group. The second outcome considers clinical scores such as NIHSS, mRS, IADL, ADL, MOCA, PHQ-9 at baseline, 90 and 180 days; tolerance and side effects of remote ischemic conditioning; the reccurence of stroke or other vascular events at 180 days; incidence of stroke-associated comorbidities and the proportion of death of any cause within 180 days.

## Introduction

Ischemic stroke is the leading cause of death and disability worldwide, being a socioeconomic problem in the 21st century, despite the treatment advances. According to the World Health Organization, stroke is the second cause of death after neoplasia. The incidence is variable depending on the country, region, and quality of medical assistance. The incidence rate of ischemic stroke among young people has increased in recent years [1].

In Romania, stroke is a public health problem, with more than 60.000 new strokes occurring every year and 200 new strokes daily. Accordingly, every 10 minutes, there is a new stroke case. One-third of these patients remain with disabilities.

Most strokes could be prevented by an efficient system of prevention, which would include strategies to educate the community about modifiable risk factors and the warning signs of a stroke.

The INTERSTROKE study – a standardized case-control study – found that hypertension, physical inactivity, poor diet, diabetes, abdominal obesity, current smoking, alcohol consumption, psychosocial factors, cardiac causes, waist to hip ratio, apolipoprotein ratio, are associated with 90.7% of all strokes [2].

The current recommended treatment for acute ischemic stroke (AIS) includes reperfusion treatment (intravenous thrombolysis, mechanical thrombectomy) and aspirin. In Romania, the reperfusion treatment has not peaked at its full potential yet. Only a small part of the population can receive reperfusion treatment due to the limited window, technical requirements and lack of recognizing stroke signs. A substantial number of stroke patients remain with a physical disability, and the burden of stroke is massive, with a significant negative impact on patients and caregivers as well as the socioeconomic status. At this moment, there is no alternative treatment available.

In the last years, some neuroprotective studies conducted on animals with good results have been published, but similar research failed in the clinical trials.

Remote ischemic conditioning (RIC) is an intervention that reduces the blood flow distally from an ischemic lesion in an attempt to minimize the ischemic injury of the organ (in stroke, in a tissue different than the brain). A mechanical tourniquet placed around a standard arm or leg will perform repetitive inflation and deflation. The mechanisms underlying this effect are neurovascular protection, anti-inflammatory action, reduced excitotoxicity, and metabolic protection [3]. RIC is a potential neuroprotective new treatment that has been demonstrated as being safe when translating from animals to clinical trials. Nevertheless, the few trials assessing its efficiency in reducing the ischemic in the injury of the brain have inconsistent results.

This study aims to explore the efficiency and safety of RIC to the arm during the first five days following AIS without the reperfusion treatment (intravenous thrombolysis, mechanical thrombectomy). We hypothesized here that RIC would reduce the infarct size (neuroprotection in the reperfusion window) and improve functional recovery.

## Material and Methods

### Design

This is a double-blind, randomized controlled multicenter trial that is performed in two hospitals from Romania (Emergency Clinical Hospital and Colentina Hospital, both located in Bucharest). It is conducted according to medical bioethics, respecting the ethical principles for medical research involving human subjects – World Medical Association (Helsinki). The study was approved by an institutional review committee, and the subjects gave full informed consent. All the patients will receive standard treatment for secondary prevention of AIS according to the guidelines of the Romanian Society of Neurology (antiplatelets, blood pressure control and cholesterol reduction therapy).

### Patient population

A total of 200 patients with AIS admitted to the emergency room are eligible for this study. The patients will be divided into two groups: One hundred will be assigned to the experimental group and 100 to the control group. This will allow the intervention to start from day 0 of hospitalization in the neurology ward.

The inclusion and exclusion criteria are listed in Table 1.

**Table 1: T1:** The inclusion and exclusion criteria.

**Inclusion Criteria**	**Exclusion Criteria**
Patients aged 50-80 years	Reperfusion treatment (intravenous thrombolysis, mechanical thrombectomy)
5 < NIHSS scores < 25	Hemorrhagic stroke on CT scan
Ischemic stroke confirmed by CT scan	5 > NIHSS scores > 25
<24 hours from onset to treatment	Fluctuating neurological deficit
Signed informed consent	Transient ischemic attack
	Other cerebral lesions: cerebral tumors, arteriovenous malformation.
	Uncontrolled blood pressure with systolic pressure < 90/60 mmHg or > 200/100 mmHg
	Difference between systolic blood pressure in the upper arms > 10 mmHg
	Ischemic events in the last 6 months (AIS, myocardial infarction and others)
	Premorbid Rankin >3
	Comorbidity with any serious diseases and life expectancy of less than 6 month

### Intervention

The subjects will be double-masked and randomized into the experimental and control group in a 1:1 ratio, according to the predefined drawing lots.

A manual tourniquet will be placed around the upper arm, contralateral to the neurological deficit (to reduce the possible local adverse events) in the first 24 hours after the diagnosis of AIS. All patients will receive five cycles of three-minute inflation of the blood pressure cuff, followed by five minutes of reperfusion. The procedure will be performed twice daily (morning and afternoon) during the first five days of hospitalization. In the experimental group, the level of cuff inflation will be >20 mmHg above the systolic blood pressure, up to 180 mmHg. The subjects in the control group will receive cuff inflation up to 30 mmHg, which will induce sham conditioning.

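### The active cuff rule cannot be met at eligible systolic pressures of 160-200 mmHg, and at 180-200 mmHg the cuff is at or below systolic (minor)

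*Protocol article*

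**What the plan says.** Three printed statements fix the active dose and who may receive it.

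- **Margin and cap (Protocol article, Intervention):** in the experimental arm "the level of cuff inflation will be >20 mmHg above the systolic blood pressure, up to 180 mmHg". The sham cuff goes to 30 mmHg.
- **Cap repeated (Abstract):** "remote ischemic conditioning twice daily with a maximum of 180 mmHg for 5 days". This settles that 180 mmHg is a maximum, not an example.
- **Entry limit (Patient population, Table 1):** the exclusion is "Uncontrolled blood pressure with systolic pressure < 90/60 mmHg or > 200/100 mmHg". Systolic pressures from 90 to 200 mmHg inclusive are therefore eligible, subject to the diastolic limits.

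The dose schedule is also in the Intervention section: "five cycles of three-minute inflation of the blood pressure cuff, followed by five minutes of reperfusion", and "The procedure will be performed twice daily (morning and afternoon) during the first five days of hospitalization". Table 1 requires "<24 hours from onset to treatment". The Design section lists blood pressure control as part of standard care for everyone, but names no systolic level that must be reached before a cuff is inflated.

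On what the cuff has to achieve, the article points two ways. The Abstract describes the treatment as "an intervention based on blood flow reduction applied at a distance from the lesion" and the Introduction as "an intervention that reduces the blood flow distally from an ischemic lesion"; both speak of reducing flow. The Intervention section ties the pressure to a level above systolic and treats deflation as reperfusion, which suggests that occlusion is intended.

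**The concern.** The cuff pressure is the dose of the only experimental treatment. The article sets that dose relative to each patient's systolic pressure, puts an absolute ceiling on it, and admits patients whose systolic pressure is above that ceiling. For part of the eligible range the operator cannot follow the rule as printed.

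If the effect depends on stopping arterial inflow, an active session with the cuff at or below systolic delivers less than intended. Across the arm this would pull the active-sham difference toward zero. It would not create a difference in favour of treatment.

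**Working it through.** **Inputs from the article.** Cuff more than 20 mmHg above systolic (Intervention); cuff at most 180 mmHg (Intervention, Abstract); eligible systolic pressure (SBP) 90-200 mmHg (Table 1); two sessions a day for five days, each of five cycles of 3 minutes' inflation (Intervention); 100 patients per arm (Patient population).

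**Step 1: where margin and cap can both hold.** Cuff > SBP + 20 and cuff ≤ 180 together require SBP + 20 < 180, so SBP < 160 mmHg.

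| SBP (mmHg) | Cuff must exceed | Cap minus SBP | Margin met? | Cuff above SBP? |
|---|---|---|---|---|
| 140 | 160 | 40 | yes | yes |
| 159 | 179 | 21 | yes | yes |
| 160 | 180 | 20 | no | yes |
| 170 | 190 | 10 | no | yes |
| 180 | 200 | 0 | no | no |
| 190 | 210 | -10 | no | no |
| 200 | 220 | -20 | no | no |

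The margin fails throughout 160-200 mmHg. The cuff fails to exceed systolic throughout 180-200 mmHg. To keep the margin at 200 mmHg the cap would have to exceed 220 mmHg; to keep the cap, entry would have to be limited to SBP below 160 mmHg.

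**Step 2: what one affected day means for a patient.** Sessions: 2 × 5 = 10 per patient, or 10 × 100 = 1,000 in the active arm. Inflation: 5 × 3 = 15 minutes per session, 15 × 10 = 150 minutes in all. A patient at 180 mmHg or above for both sessions of one day has 2 × 15 = 30 of 150 minutes (20%) with the cuff at or below systolic.

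**Step 3: what it could mean for the comparison (assumptions, illustration only).** The article gives no blood pressure distribution and shows no effect size, so both must be assumed. Take a standardised effect of 0.400, which gives 80% power with 100 per arm (two-sample t-test, two-sided 0.05). Let q be the share of active sessions at SBP 180 mmHg or above and k the share of effect those sessions keep, with effect proportional to sessions: d = 0.400 × (1 − q(1 − k)).

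| q | d if k = 0 | Power | d if k = 0.5 | Power |
|---|---|---|---|---|
| 0% | 0.400 | 80% | 0.400 | 80% |
| 2% | 0.392 | 78.8% | 0.396 | 79.6% |
| 5% | 0.380 | 76.2% | 0.390 | 78.4% |
| 10% | 0.360 | 71.7% | 0.380 | 76.2% |

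The loss is small unless such sessions are common.

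**The case against.** The best defence is that 180 mmHg is simply an overriding ceiling: the margin is a target, the cap wins, and every session can be carried out. That reading is sensible, but the article does not state it. Even on that reading, the cuff does not exceed systolic at 180-200 mmHg.

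A second defence is that few patients are affected. Table 1 limits pressure at entry, while the cuff follows systolic over five days of blood pressure control, and the diastolic limit of 100 mmHg removes some patients with high systolic pressure. This stands as a reason to expect a small effect. It does not remove the conflict: a patient at 190/95 mmHg is eligible, treatment must start early, and no systolic limit applies at inflation.

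A third defence is that the Abstract and Introduction ask only for reduced flow, so a 180 mmHg cuff may still be active, and it is far from the 30 mmHg sham. This also stands in part, which is why the consequence is put as possible rather than certain.

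A fourth is that a journal article leaves session-level handling to the full protocol or manual. That is fair as to a missing rule for high readings, and the absence of one is not the complaint. The complaint is that printed figures disagree.

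A reader might go further and infer that a null result could not be told apart from non-delivery. The article does not support that. The share affected is unknown, and in the illustrated scenarios 90-98% of active sessions have the cuff above systolic.

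**Conclusion.** The rule is wrong as written, and the error is minor. The pressure arithmetic is certain: the printed margin cannot be met at eligible systolic pressures of 160-200 mmHg. In the lower band, 160-179 mmHg, the cuff still exceeds systolic. A reader might infer that treatment fails there too, but nothing in the article shows any loss of effect. In the upper band, 180-200 mmHg, occlusion may not be achieved, and a modest dilution toward the null is possible.

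The size cannot be fixed from the article. The power figures rest on an assumed effect, an assumed proportional dose-response and assumed shares of sessions. It would also be too strong to call the comparison biased or invalid: randomisation protects it, and any dilution works against the treatment.

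**What to change.** 1. Reword the Intervention section to: *more than 20 mmHg above systolic where possible, never above 180 mmHg*. The entry criteria stay as they are.
2. Measure systolic before each session in both arms.
3. If it is 180 mmHg or above, repeat the reading later the same day and give the session once systolic is below 180 mmHg. For the first session, the retry must fall within the 24-hour treatment window. Table 1 counts this from onset and the Intervention section from diagnosis; the onset limit closes first and should govern.
4. If systolic stays at 180 mmHg or above, give the session at 180 mmHg (30 mmHg in the sham arm) and record it as below target, not as missed. Withholding it could discard active treatment: at q = 10%, a session that would have kept half its effect moves from the 76.2% cell to the 71.7% cell of the table.
5. Do not defer sessions at 160-179 mmHg.
6. Record pre-session systolic and achieved cuff pressure, keep all randomised patients in the primary analysis, and report the share of active sessions with the cuff at or below systolic.

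Make the change by dated amendment, decided without sight of outcomes by arm. Forty of 200 patients had been recruited at first submission; the present count is unknown.

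**Cost.** Two numbers per session, at most 2 × 10 = 20 per patient, some of which the case report form may already hold. The active arm needs a systolic reading anyway to set the cuff, so the added reading falls mainly on the sham arm. Some sessions will be delayed within the day. Raising the cap instead would restore the margin, but trades against tolerance and is not needed here.

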## Follow-up time

All included patients will be reevaluated clinically after three months (90 days) and 6 months (180 days) and a brain CT scan will be performed at 6 months (180 days) (Table 2).

**Table 2: T2:** Study protocol.

**Acute Ischemic stroke** **5 <NIHSS score <25 (randomized)**	**Day 0- 5**	**90 days**	**180 days**
**RIC - experimental group**	• Guideline-based treatment • RIC twice/day • NIHSS, mRS • Infarct volume	• Guideline-based treatment • NIHSS, mRS	• Guideline-based treatment • NIHSS, mRS • Infarct volume
**RIC - control group**	• Guideline-based treatment • RIC twice/day • NIHSS, mRS • Infarct volume	• Guideline-based treatment • NIHSS, mRS	• Guideline-based treatment • NIHSS, mRS • Infarct volume

## Results

The primary outcome measure will be radiological, assessing the difference of brain infarct volume measured by CT at baseline and 180 days in the experimental group versus the control group. The CT scan will be performed at day 3-4 (or at discharge) and 180 days. The baseline infarct volume will be determined as the hypodensity image on the CT scan and measured by manual outlining. The follow-up volume at 180 days will be defined by the same method. The infarct growth will be defined as the difference between the follow-up volume and the baseline volume. The radiologist will be blinded to the clinical data, and the group examined. The same CT scan protocol will be used in both centers.

The second outcome measure will be clinical and will assess the magnitude of improvement by

1.Incidence of improvement or deterioration (not due to hemorrhage transformation) of NIHSS at 90 and 180 days compared with baseline;2.Modified Rankin Scale (mRS), Instrumental Activities of Daily Living (IADL), Activities of Daily Living (ADL), Montreal Cognitive Assessment (MoCA), Patient Health Questionnaire-9 (PHQ-9) scores at 90 days and 180 days compared to baseline;3.Tolerance and side effects of RIC;4.Recurrence of stroke or other vascular events at 180 days;5.Incidence of stroke-associated comorbidities;6.The proportion of death by any cause during 180 days.

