## Discussion

To our knowledge, this is the first clinical trial to investigate the effect of RIC after a stroke by measuring the ischemic volume on the CT scan.

The primary outcome measure in our study will be radiological, showing the difference in brain infarct size volume between the experimental group and the control group. In the STAIR Group 2016 (Stroke Treatment Academic Industry Roundtable [4]), the infarct volume has been chosen as the radiological objective outcome, being linked to the clinical outcome [5].

The clinical outcome measure will be investigated as a second target using multiple validated scales: NIHSS, Rankin, Barthel, IADL, ADL. All these reflect the quality of life of a stroke survivor. Also, impaired scores are associated with poorer medical health, increasing medical costs. We will also investigate the cognitive status (MoCA test) and depression (PHQ-9 test) comparing the two groups at baseline, at 90 days, and 180 days.

Our study differs in some respects compared to previous ones. Firstly, it is a multicentre study, including patients from 2 hospitals. Secondly, all the patients will have an ischemic stroke confirmed on the CT scan. Previous studies assessed the brain infarct volume on MRI (REPOST study [6], RESCUE study [7], RECAST study [8], Hougaard’s study [9], Meng’s study [10], Mi’s study [11], Wang’s study [12]). Thirdly, we will include moderate and severe stroke patients (NIHSS= 5-25). Previous studies included either mild-moderate (NIHSS= 0-15) [10,13] or any stroke severity [9]. Fourthly, we will include all ischemic stroke subtypes, according to the TOAST classification. Fifthly, we will measure the final infarct volume at 180 days (6 months). Previous studies measured the final infarct volume at 24 hours [7, 9] or day 4 [6]. Finally, there are different types of RIC procedures in the previous studies: sites of limb conditioning: arm, leg, both arms, both legs; cycles and duration of inflation/deflation; timing of RIC; frequency: once or repeated /day.

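### The baseline infarct volume in the primary change score comes from a CT at day 3-4 or discharge, during or after treatment, so the score subtracts out any early benefit

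*Protocol article*

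**What the plan says.** The Results section of the article sets the primary outcome as "assessing the difference of brain infarct volume measured by CT at baseline and 180 days in the experimental group versus the control group". The scan times follow at once: "The CT scan will be performed at day 3-4 (or at discharge) and 180 days". The same section says how the first volume is read, "The baseline infarct volume will be determined as the hypodensity image on the CT scan and measured by manual outlining", and how the two are combined: "The infarct growth will be defined as the difference between the follow-up volume and the baseline volume".

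Treatment begins before the earlier scan. Under Patient population, the article says of the allocation to two groups: "This will allow the intervention to start from day 0 of hospitalization in the neurology ward". Under Intervention it says: "The procedure will be performed twice daily (morning and afternoon) during the first five days of hospitalization".

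Three other places bear on the point:

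- Table 1 requires "Ischemic stroke confirmed by CT scan" as an entry criterion, so an earlier CT exists. Nothing says that its volume is the baseline.
- Table 2 lists the first infarct volume in the column for days 0 to 5, beside the conditioning sessions.
- The Discussion words the primary outcome as a between-group difference in infarct volume, with the final volume taken at 180 days, and mentions no change from baseline.

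**The concern.** The Introduction's hypothesis is that conditioning makes the infarct smaller through neuroprotection in the reperfusion window, which is an early effect. A reference value measured on day 3-4 or at discharge may already carry that effect. It is then an outcome of treatment and not a baseline. Subtracting it from the 180-day volume removes whatever benefit had accrued by then and leaves only the part that appears later.

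The allowance for a discharge scan adds a second problem. Discharge day can depend on recovery, and recovery may depend on treatment, so the timing of the reference scan may differ between arms.

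At stake is the primary comparison. If the intervention works as hypothesised, the analysis as written would tend to understate the benefit, and it could miss the benefit altogether.

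**Working it through.** The article gives no alpha, power, effect size, SD or expected volume, so there is no stated calculation to reproduce. Only the session count rests on the article's figures. Every mL and power figure below rests on assumptions.

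**1. Sessions completed before the first named CT.** The total is 2 per day × 5 days = 10. For a scan on day *d* with treatment starting on day *s*, the number completed lies between 2(*d* − *s*) (scan before the morning session) and 2(*d* − *s* + 1) (scan at the end of the day).

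| Treatment starts on | Scan on day 3 | Scan on day 4 |
|---|---|---|
| day 0 | 6-8 of 10 | 8-10 of 10 |
| day 1 | 4-6 of 10 | 6-8 of 10 |

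If a patient misses the first morning session, the ranges are 5-9 of 9 counting from day 0 and 3-7 of 9 counting from day 1. Under every count the scan falls during or after treatment.

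**2. What the change score estimates.** Let *B* and *F* be mean control volumes at day 3-4 and day 180. Let *r* be the proportional reduction with conditioning at day 180, and *q* the share of that reduction already present at day 3-4.

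- Difference in final volume (conditioning minus control): −*rF*.
- Difference in change score: −*rF* + *qrB*.
- The sign reverses when *q* > *F*/*B*, which requires *F* < *B*.
- If the effect is instead a fixed amount in mL, the difference in change is −(1 − *q*)*rF*. It shrinks toward zero but never reverses.

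**3. Illustration.** Assumed: *B* = 50 mL, *r* = 20%, SD 25 mL for either endpoint, two-sided alpha 0.05. The 100 per arm is from the article. The standard error is 25 × √(2/100) = 3.54 mL, and power is about Φ(|difference|/3.54 − 1.96).

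| *F* (mL) | Difference in final volume | Difference in change, *q* = 0.8 | Difference in change, *q* = 1 |
|---|---|---|---|
| 35 | −7 mL (power 51%) | −7 + 8 = +1 mL | −7 + 10 = +3 mL |
| 50 | −10 mL (81%) | −10 + 8 = −2 mL (8%) | 0 mL |
| 60 | −12 mL (92%) | −12 + 8 = −4 mL (20%) | −12 + 10 = −2 mL (8%) |

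With a truly pre-treatment baseline (*q* = 0), the difference in change equals the difference in final volume in every row. The SD of a change score could differ from 25 mL, which would alter the power figures but not the differences.

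**4. Conditions for a reversal.** Suppose tissue volumes of 50 mL (control) and 35 mL (conditioning), a day 3-4 scan that reads 1.3 times tissue volume (swelling), and a 180-day scan that reads 0.9 times (shrinkage). The changes are 45 − 65 = −20 mL and 31.5 − 45.5 = −14 mL. The conditioning arm has 13.5 mL less final infarct but looks 6 mL worse on growth.

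A simulation used the same factors, log-normal volumes (median 25 mL, log-SD 1.2), a 30% reduction complete by day 3-4, and 100 per arm. It gave a significant result in the wrong direction in about 10% to 54% of trials. The low end is a t-test with measurement noise of log-SD 0.4 per scan, and the high end is a rank test with almost no noise. With stable volumes and the effect complete by day 3-4, the expected difference in change is 0 mL. With stable volumes and 70% of the effect early, t-test power is about 46%, but the estimate keeps only 30% of the effect.

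**The case against.** The best defence is that the entry CT was meant as the baseline. Table 1 requires one, the Abstract and Results use the word baseline, Table 2 allows a first volume anywhere in days 0 to 5, and an article condenses its protocol. This may be the intention. But the Results section does not say so: it names two scan times, neither before treatment, and the day 3-4 scan would then have no stated purpose. Even on this reading the text needs correcting, so the point stands as written.

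Three stronger inferences are tempting, and the documents do not support them.

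- *The sign will reverse.* This needs volumes that fall between the scans and an early effect roughly proportional to volume. The article gives no volumes and no swelling or shrinkage factors.
- *The trial cannot test its hypothesis.* The 180-day volume is collected in both arms, and functional recovery is assessed separately by clinical scales. The fault lies in one derived variable.
- *Most sessions always precede the scan.* This follows if the first treatment day is day 0. Counting from day 1, an early day-3 scan could follow only 4 of 10.

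It is also fair to say that the change score is not always weak. If much of the effect arises after day 3-4, it can detect that part. It still leaves out the earlier part, which is the part hypothesised.

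**Conclusion.** The point holds as a defect in a stated rule, not as a missing detail. Read literally, the primary outcome subtracts a post-randomisation, on-treatment measurement, and the share of any benefit present at that scan is lost. The bias is toward no effect, by *qrB* under a proportional effect or *qrF* under a fixed one.

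That the reference scan comes after treatment has begun rests on the article's own scan times and treatment start. The size does not: all mL and power values depend on assumed volumes, SD, measurement noise and early share. Reversal of sign is a conditional possibility only. The Discussion's different wording of the primary outcome is a further inconsistency to resolve. This should be corrected before any comparison by arm.

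**What to change.** Reconcile the primary outcome across the Abstract, Table 2, Results and Discussion.

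**Preferred.** Make infarct volume at 180 days the primary outcome and compare it directly between arms on a scale that tolerates zeros, such as the cube root. Adjust only for values fixed before treatment: admission NIHSS, age, centre and onset-to-treatment time.

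**Alternative.** Keep the change score, but define baseline as the eligibility CT done before the first inflation. This depends on the lesion being measurable on a scan within 24 hours of onset. The article does not say that it is, nor that this scan followed the common CT protocol.

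**In either case.** Relabel the day 3-4 volume as an early post-randomisation outcome, set one study day for it, and remove the discharge option. Neither subtract this volume nor adjust for it in the primary analysis: adjustment would also condition on something that treatment may have changed.

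**Cost.** This is a documented amendment of the primary endpoint, made before any unblinded look, with 40 of 200 patients already recruited when the article was first submitted. No new scan is needed. The preferred option can be applied to those 40 without change, since the 180-day scan is already planned for them.

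### The primary outcome subtracts an on-treatment day 3-4 lesion outline from a 180-day outline, so it mixes swelling, contraction and growth and need not follow a reduction in infarct size

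*Protocol article*

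**What the plan says.** The Results section of the protocol article fixes the primary outcome in full.

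- **Comparison:** "assessing the difference of brain infarct volume measured by CT at baseline and 180 days in the experimental group versus the control group".
- **Scan times:** "The CT scan will be performed at day 3-4 (or at discharge) and 180 days".
- **Early volume:** "The baseline infarct volume will be determined as the hypodensity image on the CT scan and measured by manual outlining".
- **Late volume:** "The follow-up volume at 180 days will be defined by the same method".
- **Score:** "The infarct growth will be defined as the difference between the follow-up volume and the baseline volume".

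The Intervention section adds: "The procedure will be performed twice daily (morning and afternoon) during the first five days of hospitalization". A scan at day 3-4 therefore falls while treatment is still running, and a scan at discharge also comes after treatment has begun. The Introduction states the hypothesis as a smaller infarct and better functional recovery. The article nowhere mentions swelling, contraction or a correction for either.

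**The concern.** A hypodensity outline in the first days can include swollen tissue. At 180 days the swelling has resolved, and the infarct may have contracted into a cavity. The same outlining rule then captures two different quantities, and their difference is not growth of the infarct alone.

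This matters for the comparison because the early scan is not a true baseline. Treatment has already had days in which to change it. Any effect that lowers the early volume, whether less swelling or a smaller infarct by day 3-4, is subtracted from the score. A treatment that works early can then show less shrinkage than control, which the score reads as more growth. The primary result could move against the trial's own hypothesis, and a null result could not be read as no effect on infarct size.

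**Working it through.** The plan states no figure on this point, so there is none to reproduce. The check applies its own formula.

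**Inputs from the article:** the two scan times, the raw outline at both, and growth as follow-up minus baseline (Results); treatment over five days (Intervention).

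**Assumed inputs, because the article gives none:** true infarct volume I; swelling fraction e at the early scan, 0.10 to 0.40; contraction fraction s by 180 days, 0 to 0.30; no true growth after day 3-4 unless stated.

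**Step 1: what the score compares.** Let E be the early volume and F the 180-day volume, with R for RIC and C for control. Growth is G = F − E, so

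G_R − G_C = (F_R − F_C) − (E_R − E_C).

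The hypothesis concerns the first bracket. The second vanishes in expectation if E is measured before treatment, because randomisation balances it. Here E is measured on treatment, so it need not vanish. RIC scores worse whenever its early reduction exceeds its 180-day reduction.

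**Step 2: equal infarcts, different swelling.** With E = I(1 + e) and F = I(1 − s), G = −I(s + e). With s equal in both arms, the between-arm difference is I(e_C − e_R), whatever the value of s.

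| I (mL) | e_C | e_R | RIC minus control (mL) |
|---|---|---|---|
| any | equal | equal | 0 |
| 30 | 0.20 | 0.10 | +3 |
| 50 | 0.20 | 0.10 | +5 |
| 80 | 0.40 | 0.20 | +16 |

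In full for 50 mL with s = 0.20: control goes from 60 to 40 mL (−20) and RIC from 55 to 40 mL (−15). RIC appears 5 mL worse with the same final volume.

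**Step 3: smaller infarct under RIC, equal swelling and contraction fractions.** Take 80 against 100 units by day 3-4. The score differs by (100 − 80)(s + e) = 20(s + e): +2 units at e = 0.10, s = 0, and +14 at e = 0.40, s = 0.30. It is 0 only if both fractions are 0. The 180-day volumes differ by −20(1 − s), that is −20 to −14 units, in RIC's favour. The score points the other way.

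**Step 4: when a real benefit outweighs this.** In the 50 mL example the early volumes differ by 5 mL. The score favours RIC once its 180-day volume is more than 5 mL below control, that is under 35 against 40 mL.

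**Step 5: how much true growth the score can hide.** If the infarct truly grows by a fraction g after day 3-4, the score is zero when (1 + g)(1 − s) = 1 + e, so g = (1 + e)/(1 − s) − 1. This is 1.10/1.00 − 1 = 10% at the low end and 1.40/0.70 − 1 = 100% at the high end.

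**The case against.** Several stronger readings are tempting, and the article does not support them.

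- **That the score is mostly swelling resolution, or negative in most patients.** The article gives no size for swelling, contraction or later growth. The Discussion notes that earlier trials took the final volume at 24 hours or day 4, which suggests little growth remains after this trial's early scan. That is an inference, not a figure.
- **That an arm with less swelling must look worse.** This holds when 180-day volumes are about equal. Step 4 shows that a large enough benefit at 180 days reverses it.
- **That this is purely a measurement fault, separate from scan timing.** Step 1 shows otherwise. With a pre-treatment scan the same raw outline would give no between-arm bias in expectation. What would remain is a misnamed quantity.
- **That RIC is known to reduce swelling.** The Abstract says: "The mechanism is supposed to elicit neurovascular protection, anti-inflammatory action, reduced excitotoxicity and metabolic protection". Swelling is not named. An effect on it is plausible from that list, but the range must include 0 mL.

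It can also be said that a journal article leaves reading rules, such as how to outline a cavity, to a manual. That is fair for the cavity, and its absence is no fault in itself. It does not excuse the rest: the article states the scan times, the common method and the subtraction, and followed exactly they give the score examined here.

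Finally, one might take baseline to mean the admission CT, since inclusion requires a CT-confirmed stroke. That would remove the problem, but for the volume measurement the Results section names only the day 3-4 (or discharge) and 180-day scans.

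**Conclusion.** The concern holds as a fault in the stated definition of the primary outcome. The raw difference combines swelling resolution, contraction and true growth, and its early term is open to treatment effects, so it does not measure the hypothesised reduction in infarct size.

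For equal infarcts and equal contraction, the artefact against RIC runs from 0 mL (swelling unaffected) to about 16 mL (80 mL infarct, swelling 40% against 20%). If the infarct itself is 20% smaller by day 3-4, the score can favour control by 2 to 14 units per 100 over the assumed ranges. All these sizes rest on assumed swelling and contraction. The article gives no standard deviation or target difference, so they cannot be set against noise or turned into a loss of power. The identity in Step 1 needs no assumed values.

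**What to change.** 1. Make the between-arm comparison of 180-day infarct volume the primary analysis. The Discussion already treats this as the final infarct volume.
2. Adjust it for a pre-treatment measure already collected, such as baseline NIHSS taken before the first inflation. Do not adjust for the day 3-4 volume, which treatment may have changed.
3. State that the cavity counts as infarct in the 180-day outline.
4. Report the day 3-4 volume and the raw change as descriptive or secondary, and stop calling the raw difference infarct growth.

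This uses scans already planned and costs almost nothing. The price is some precision, since NIHSS is likely to predict final volume less well than an early volume would. Contraction also still lowers the absolute 180-day volumes, although equal contraction fractions in the arms do not reverse the comparison.

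A correction for swelling and tissue loss that uses the opposite hemisphere as reference, on the same CTs, can serve as a sensitivity analysis. It adds reading time and noise, especially for small or infratentorial lesions. The exclusion criteria bar ischemic events only within the last 6 months, so older infarcts may also distort it. As an illustration, with an assumed 500 mL per hemisphere and independent outlining errors of 1% to 2%, the error of the subtraction is √2 × 5 to √2 × 10, about 7 to 14 mL per scan. That is of the same order as the artefact, so the correction is better kept out of the primary analysis.
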